**Schedule for Data Collection in Clinical Study**

| **Collection  Schedule**  **Collection Items** | **Baseline** | **Follow-Up Visits  (Option, ☎)** | **Follow-Up Visits** | **Follow-Up Visits  (Option, ☎)** | **Close-Out Visit (COV)** |
| --- | --- | --- | --- | --- | --- |
|  | Visit 1 | Visit 2 | Visit 3 | Visit 4 | Visit 5 |
|  | 0 day | Week 6  (±2 Weeks) | Week 12 (±2 Weeks) | Week 18 (±2 Weeks) | Week 24 (±2 Weeks) |
| Obtain Written Consent^1)^ | ○ |  |  |  |  |
| Inclusion/Exclusion Criteria Confirmation | ○ |  |  |  |  |
| Assignment of Randomization Number | ○ |  |  |  |  |
| Installation of Well Check and Link to Institution | ○ |  |  |  |  |
| Demographic Information^2)^ | ○ |  |  |  |  |
| Information on Type 2 Diabetes^3)^ | ○ |  |  |  |  |
| Medical History Survey^4)^ | ○ |  |  |  |  |
| Alcohol/Smoking/Lifestyle Habits^5)^ | ○ | (○) | ○ | (○) | ○ |
| Physical Measurement^6^ | ○ | (○) | ○ | (○) | ○ |
| Vital Signs^7)^ | ○ | (○) | ○ | (○) | ○ |
| Body Composition Analysis (InBody) Test ^8)^ | (○) | (○) | (○) | (○) | (○) |
| Prior/Concomitant Medications^9)^ | ○ | (○) | ○ | (○) | ○ |
| Laboratory Tests^10)^ | ○ | (○) | ○ | (○) | ○ |
| Frequency of Well Check Use (Number of Login Days) |  |  |  |  | ○ |
| Well Check Usage Satisfaction Survey^11)^ |  |  |  |  | ○ |

*There are no additional visits or laboratory tests conducted specifically for this clinical study. In a routine clinical setting, it is recommended to collect data at 6-week intervals from Visit 1 (Baseline, Day 0) to 24 weeks (Visit 2: 6 weeks, Visit 3: 12 weeks, Visit 4: 18 weeks, Visit 5: 24 weeks). Visit 2 (6 weeks) and Visit 4 (18 weeks) can be optional visits and data can be collected via phone calls, based on the investigator (responsible physician )'s discretion. If a subject withdraws or drops out from the study, the data collected up to that point should be recorded in the case report form to the maximum extent possible.

1. Written consent must be obtained before performing any clinical study procedures. The date of written consent and Visit 1 (Baseline, Day 0) may differ, but consent must be obtained before participation in the clinical study.
2. Collect demographic information [initials, gender, age (month and year of birth), pregnancy and breastfeeding status].
3. Collect information on Type 2 Diabetes (date of diagnosis).
4. Collect medical history within 6 months prior to Visit 1 (Baseline, Day 0).

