## Rationale

Based on the pilot study results, the difference in average HbA1c between the test group and the control group after 24 weeks of using Well Check in Type 2 Diabetes patients was considered to be 0.4% (8.0% vs. 7.6%), with a standard deviation (*s*) of 1.1%. Referring to these results, the total sample size (*n*) required was estimated to be approximately 274 subjects using G*Power 3.1.9.7.

Since this study employs cluster randomization, we further adjusted the sample size calculation by incorporating the design effect to account for potential intra-cluster correlations among patients within the same clinic. We calculated the design effect using the standard formula:

$$Design effect=1+\left( m-1 \right)\times ICC$$

Referring to previous studies conducted in primary care settings for patients with type 2 diabetes [11, 12], we conservatively adopted an intraclass correlation coefficient (ICC) value of 0.02 and assumed an average cluster size (*m*) of 20 participants per center. Therefore, we calculated the resulting design effect to be 1.38, and applying this adjustment to the initial sample size estimate gives a revised total sample size of 378 participants. Finally, considering an anticipated dropout rate of approximately 20%, we adjusted the target recruitment number further to approximately 480 participants.

[figure not shown]

< Calculation for Subject Number – Based on Glycated hemoglobin>

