### Safety Analysis Set

Subjects who meet the inclusion/exclusion criteria, have been enrolled in this study, received the investigational product at least once according to the approved indications, and have undergone safety evaluations will be included in the safety analysis set.

1. **Methods of Analysis**
2. **General Principles**

Continuous variables will be presented as descriptive statistics (number of subjects, mean, standard deviation, median, minimum, maximum), and categorical variables will be presented as frequencies and percentages. Unless otherwise specified, all tests will be two-sided with a significance level of 5%. All p-values will be reported to a maximum of three decimal places. If not exactly divisible, values will be rounded to two decimal places, rounding up at the third decimal place.

If missing data is minimal and evenly distributed, a complete-case analysis will be considered; multiple imputation methods will be employed if missing data is substantial or disproportionately distributed between groups. Sensitivity analyses will also be performed to ensure the robustness and validity of conclusions under various missing-data scenarios.

1. **Demographic and Baseline Characteristics**

For the demographic data (age, gender, etc.) and baseline characteristics of the study subjects, continuous variables will be presented as mean, standard deviation, median, minimum, and maximum values, while categorical variables will be presented as frequency and percentage.

To assess baseline comparability between intervention and control groups, standardized mean differences (SMDs) will be calculated for key baseline characteristics, including age, sex, HbA1c, BMI, and diabetes duration. Variables exhibiting significant imbalance between groups (SMD > 0.1) will be included as covariates in subsequent analyses.

1. **Efficacy Endpoints**

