### Primary Efficacy Endpoints

For the change and percent change in HbA1c, descriptive statistics will be presented at baseline and at 24 weeks. The change from baseline to 24 weeks will be analyzed using mixed-effects models or generalized estimating equations (GEE) to account explicitly for clustering effects. Patient-level covariates identified as significantly imbalanced at baseline (SMD > 0.1) will be included as fixed effects, and inter-center variability as random effects.

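### The primary handling of missing 24-week HbA1c is chosen from the observed amount and balance of missingness, with no cut-offs or missingness assumption; one method should be fixed in advance

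*Protocol*

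**What the plan says.** Under General Principles in Section 7.2, the protocol gives two branches: "If missing data is minimal and evenly distributed, a complete-case analysis will be considered; multiple imputation methods will be employed if missing data is substantial". The second branch in full is: "multiple imputation methods will be employed if missing data is substantial or disproportionately distributed between groups". It then adds: "Sensitivity analyses will also be performed to ensure the robustness and validity of conclusions under various missing-data scenarios". It gives no figure for any of the limits, names no missingness mechanism and does not describe the sensitivity scenarios.

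The primary analysis is described separately: "The change from baseline to 24 weeks will be analyzed using mixed-effects models or generalized estimating equations (GEE) to account explicitly for clustering effects". The random effect mentioned there is for the centre, and the outcome is the single change to week 24.

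Three other parts bear on the point.

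- **Expected loss.** Section 3.2 plans for it: "considering an anticipated dropout rate of approximately 20%, we adjusted the target recruitment number further to approximately 480 participants".
- **Intermediate HbA1c.** The data collection schedule says "Visit 2 (6 weeks) and Visit 4 (18 weeks) can be optional visits and data can be collected via phone calls", so week 12 is the one intermediate visit not marked optional. Laboratory results are collected only if obtained in routine care.
- **Efficacy set.** Section 7.2 admits only patients with some post-baseline HbA1c.

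**The concern.** Two features of the rule are weak.

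**The primary method depends on the data.** The choice is made after missingness by arm is known, in a trial whose clinics know their own allocation. Complete-case analysis is only to be considered, and even but moderate missingness falls clearly into neither branch. Two analysts could follow the text faithfully and report different primary results.

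**Balance is the wrong test.** Equal dropout rates do not make the remaining patients comparable when the reasons for leaving differ. The protocol makes different reasons plausible. In Section 4.4, test-arm patients are asked to record glucose daily, their physician reviews alerts weekly, and those who do not measure receive monthly encouragement. Control patients get the automatic educational material but no specific guidance and no physician monitoring through the app. Section 3.5 lists failure to follow instructions about the software as a ground for withdrawal. It is written for all subjects, but it bears mainly on the arm that receives such instructions.

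A complete-case analysis of the change also ignores an HbA1c already collected at week 12 from patients who later lack week 24. Calling the primary model a mixed-effects model does not help: with one change score per patient and a centre effect, a patient without week 24 contributes nothing.

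**Working it through.** **1. The plan's own figures.** Section 3.2 gives a difference of 0.4, SD 1.1, ICC 0.02 and 20 patients per centre. Design effect = 1 + (20 − 1) × 0.02 = 1.38. Then 274 × 1.38 = 378, and 378 / 0.80 = 472.5, so 473, close to the stated 480 (24 clinics × 20). The chain reproduces. Choosing another missing-data method does not alter it.

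**2. Can the complete-case branch be reached with 20% dropout?** At 20%, 96 of 480 patients lack week 24 and 384 have it. The efficacy set keeps only those of the 96 with an earlier post-baseline HbA1c. That share is not given, so a range is assumed:

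- a quarter: 24 / (384 + 24) = 5.9% missing within the set
- a half: 48 / (384 + 48) = 11.1%
- all: 96 / 480 = 20%

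The protocol does not say whether missingness is judged within the set or among all enrolled. If within the set, a figure that might be called minimal is possible.

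**3. Bias at equal rates, general form.** If dropouts in one arm differ from that arm's completers by k in week-24 change, and a fraction d is missing, the completers' mean is off by d × k. For k from 0.25 to 1.0 (assumed), this is 0.005–0.02 at d = 2%, 0.013–0.05 at 5% and 0.025–0.10 at 10%. If the other arm is off by the same amount in the same direction, the difference between arms is unaffected.

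**4. A specific mechanism.** Assumptions not in the protocol: correlations of HbA1c of 0.7 (baseline with week 12), 0.6 (baseline with week 24) and 0.8 (week 12 with week 24). Test-arm dropout is logistic in the standardised week-12 change Z, with log-odds b = 0.7 or 1.0 per SD. Control dropout is random at the same rate.

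- Variance of the week-12 change = 1.1² × 2 × (1 − 0.7) = 0.726
- Covariance of the week-12 and week-24 changes = 1.1² × (0.8 − 0.7 − 0.6 + 1) = 0.605
- Week-24 change per unit of Z = 0.605 / √0.726 = 0.710
- Bias = 0.710 × |mean Z among test-arm completers|, with the logistic intercept solved numerically to give rate d

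| Missing in each arm | Mean Z of completers (b = 0.7; 1.0) | Bias | Share of 0.4 | Type I error (simulated) |
| --- | --- | --- | --- | --- |
| 2% | −0.014; −0.019 | 0.010; 0.014 | 2–4% | about 5% |
| 5% | −0.034; −0.047 | 0.024; 0.033 | 6–8% | 5–6.5% |
| 10% | −0.067; −0.091 | 0.047; 0.064 | 12–16% | 7–10% |
| 20% | −0.130; −0.173 | 0.092; 0.123 | 23–31% | 12–21% |

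Type I error comes from separate simulations of 24 clinics of 20 with no true effect, tested by a t-test on clinic means (22 df). Simulated biases scatter around the values shown: 0.02–0.04 at 5% and 0.04–0.06 at 10%.

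**5. Variations.**

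- With the same outcome-related mechanism and equal rates in both arms, a true difference of 0.40 is estimated as 0.398–0.399.
- If test-arm dropout depends on the week-12 level rather than the change, the bias at 20% falls to 0.01–0.02 for the change score and is 0.05–0.07 with baseline adjustment.
- An analysis that uses week-12 HbA1c has bias of about 0.005 or less in these scenarios. This follows from how they were built, since dropout there depends only on observed values.

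**The case against.** The strongest reply is that the rule is more careful than it first appears. A reader might infer that it treats equal rates as sufficient. It does not: complete-case analysis needs missingness to be both small and even, and either substantial or uneven missingness leads to multiple imputation. A reader might also attach the 20% row of the table to the planned 20% dropout. On an ordinary reading 20% is substantial, so imputation would apply, and that row is only an upper bound. Both corrections stand.

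The direction and strength of the bias also rest on an assumed mechanism. The protocol shows that management differs by arm. It does not show who drops out or why. That stands too, so the claim is that the rule can bias the result, not that it will.

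Sensitivity analyses are promised. They help interpretation, but they are unspecified and do not settle which result is primary.

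Thresholds and imputation models are often left to the statistical analysis plan, and their absence here is not the point. The protocol itself fixes a conditional switch, and a later document that named a single method would depart from it. The switch turns on amount and balance, which can be judged without seeing treatment effects. That reduces the risk of selective choice but does not make balance a valid criterion.

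**Conclusion.** The point holds in a limited form. The switch depends on the data, has no cut-offs, and uses balance between arms in place of a stated missingness assumption. In the branch where complete-case analysis is a realistic choice, the bias is about 0.01 at 2% missing, 0.02–0.04 at 5% and 0.04–0.06 at 10%, with type I error of about 5%, 5–6.5% and 7–10%. These figures need dropout that is related to response in one arm and not in the other, plus the assumed correlations and slopes. With a common mechanism the bias is about zero. The documents do not support saying that the trial's result will be biased, or that the planned dropout rate implies a bias of a quarter of the effect. The change is still worth making, because a better method is available at almost no cost.

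**What to change.** Replace the conditional sentence in Section 7.2 with one primary analysis that applies whatever the missingness. Either of two choices would do.

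- **Mixed model.** A likelihood-based linear mixed model on all collected post-baseline HbA1c values (weeks 12 and 24, and weeks 6 and 18 where measured), with arm-by-visit terms, baseline HbA1c, a clinic random effect and within-patient correlation. The treatment effect is the week-24 contrast.
- **Multiple imputation in every case.** Done by arm, with baseline HbA1c, week-12 HbA1c where measured, and clinic in the imputation model.

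State the missing-at-random assumption. Keep complete-case as a sensitivity analysis, and add one that departs from missing at random by giving test-arm dropouts control-like or worse values.

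The cost is a few sentences and some programming, with no extra patients, visits or tests and no change to the sample size. The model is slightly more complex. It does not remove bias from dropout driven by the unseen week-24 value, and it gains little for patients with no week-12 HbA1c.

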## Study Completion and Withdrawal/Dropout

1. **Subject’s Completion and Termination of Study Participation**

A subject is considered to have completed the study upon completing the follow-up visit procedures at the 24-week point after their first visit (baseline). The study is deemed complete when the last subject finishes their study participation.

1. **Subject’s Withdrawal/Dropout of Study Participation**

Subjects can discontinue their participation in the study at any time at their discretion. The investigator or sponsor can also withdraw/drop a subject’s participation at any time for safety, behavioral, or administrative reasons. The following are conditions under which a subject might be withdrawn/dropped from the study, and the investigator shall enter the collected study data into the eCRF up to the point of withdrawal/dropout:

1. A subject not meeting the inclusion/exclusion criteria was discovered during the clinical study
2. Withdrawal by subject (or his/her legal representative)
3. Non-Compliance with Investigational Product

: Subjects do not agree to or follow the investigator’s instructions related to the investigational software.

1. Lost to follow-up

: Subjects cannot be contacted for follow-up.

1. Physician Decision

If a subject is withdrawn/drops out, the investigator must notify the sponsor and make every effort to complete the end-of-study evaluation. The reasons for withdrawal/dropout must be documented in the source document and the eCRF.

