# Clinical Study Method

## Overall Study Design

This clinical study is designed as a primary care-based, prospective, multicenter, cluster-randomized, pragmatic clinical trial to confirm the improvement effects on blood glucose, blood pressure, and weight over 24 weeks in patients with Type 2 Diabetes when using ‘Well Check’ with or without investigator-linked management in real-world primary care settings.

Eligible subjects include patients currently being treated with Envlo Tab. or Envlomet SR Tab. for Type 2 Diabetes or those deemed eligible for such treatment by the investigator (responsible physician). Subjects must also be able to use the digital healthcare smartphone application without difficulty.

Due to the practical constraints of primary care settings, where it is challenging to manage test group and control groups separately within the same institution, cluster randomization will be used. Institutions will be randomized as either the test group [institutions managing subjects with the 'Well Check' app in conjunction with the investigator (responsible physician)] or the control group (institutions where subjects use the 'Well Check' app for self-management). The study will be conducted following this setup.

[figure not shown]

Study Subjects

Use of 'Well Check'
for Simple Self-Management

(Control Group Institutions)

Investigator
(Responsible Physician)

Use of 'Well Check'
for Integrated Management
(Study Group Institutions)

Cluster Randomization

Participating Institutions

(Primary Care Institutions)

Figure 1. Clinical Study Design

Data collection for this clinical study will be based on medical records documented during routine clinical visits. Collected data will include demographic information, physical measurements, vital signs, and laboratory test results. There are no mandatory visits, tests, or treatments specified by this study.

However, prospective data collection through follow-up visits will be conducted up to 24 weeks from the baseline registration date.

The planned time points for prospective data collection are baseline (0 days), visit 2 (6 weeks), visit 3 (12 weeks), visit 4 (18 weeks), and visit 5 (24 weeks). Visits 2 and 4 can be optionally collected based on the investigator (responsible physician)'s judgment and allow for telephone follow-ups.

[figure not shown]

Visit 1

(0 days)

Visit 2

(6±2 weeks)

Visit 3

(12±2 weeks)

Visit 4

(18±2 weeks)

Visit 5

(24±2 weeks)

Baseline

Follow-Up Visits

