## Study Procedure and Schedule

### Visit Schedule

There are no mandatory visits, tests, or treatments specified by this study. Data will be prospectively collected using medical records, investigator assessments, and laboratory test results from routine clinical visits. Each investigator will collect predefined information from subjects at baseline and during the follow-up period.

1. **Visit 1 (Baseline, Day 0)**

At the first visit (baseline), the following information will be collected:

- Obtain subject consent and assign subject enrollment number
- Inclusion/Exclusion Criteria Confirmation
- Installation and Hospital Integration of the Digital Healthcare Smartphone Application ‘Well Check’
- Demographic information [initials, gender, age (month and year of birth), pregnancy and breastfeeding status].
- Information on Type 2 Diabetes (Diagnosis date)
- Medical history (Past medical history within 6 months prior to enrollment (excluding the target disease) and current medical history)
- Alcohol/Smoking/Lifestyle information
- Physical measurements (height, weight, BMI)
- Vital signs (systolic/diastolic blood pressure, pulse rate)
- Body composition analysis (include skeletal muscle mass, body fat mass, body fat percentage, muscle mass, waist/hip circumference, body water, intracellular water, extracellular water, extracellular water ratio, abdominal fat percentage, etc.)
- Prior medications (diabetes treatments within 4 weeks prior to enrollment) and concomitant medications (all medications, including diabetes treatments, taken at the time of enrollment).
- Laboratory tests (HbA1c, FPG, Total Cholesterol, LDL-C, HDL-C, Triglyceride, ALT, AST, Creatinine, e GFR, UACR, UGCR, etc.)

1. **Follow-Up Visits**

Follow-up visits will be conducted at 6-week intervals from the first visit (baseline) as Visit 2 (6 weeks ±2 weeks), Visit 3 (12 weeks ±2 weeks), Visit 4 (18 weeks ±2 weeks), and Visit 5 (24 weeks ±2 weeks). Visits 2 and 4 may be optional and data collection can be conducted via phone calls, based on the investigator (responsible physician)’s discretion. During follow-up visits, the following information will be collected:

- Alcohol/Smoking/Lifestyle information
- Physical measurements (weight, BMI)
- Vital signs (systolic/diastolic blood pressure, pulse rate)

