### Efficacy Analysis Set

Subjects who meet the inclusion/exclusion criteria, have been enrolled in this study, received the investigational product at least once, and have had their HbA1c level collected post-baseline will be included in the efficacy analysis set.

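### The only efficacy set excludes patients with no post-baseline HbA1c, so the missing-data rule as written need not count or impute them

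*Protocol*

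**What the plan says.** The Efficacy Analysis Set paragraph in section 7.2 asks for eligibility, enrolment and at least one use of the product, and closes by saying that subjects who "have had their HbA1c level collected post-baseline will be included in the efficacy analysis set". No visit is named. The only other set defined is for safety; there is no full or intention-to-treat set.

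General Principles, in the same section, then gives the missing-data rule: "If missing data is minimal and evenly distributed, a complete-case analysis will be considered"; otherwise "multiple imputation methods will be employed if missing data is substantial or disproportionately distributed between groups". It adds: "Sensitivity analyses will also be performed to ensure the robustness and validity of conclusions under various missing-data scenarios". None of these sentences names the population in which missingness is judged, imputed or varied.

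The primary analysis is of change in HbA1c from baseline to week 24, by mixed model or GEE (Primary Efficacy Endpoints). On data collection, the Visit Schedule says "There are no mandatory visits, tests, or treatments specified by this study", and Overall Study Design says "Visits 2 and 4 can be optionally collected based on the investigator (responsible physician)'s judgment and allow for telephone follow-ups". The laboratory note to the data collection schedule takes results only where routine care produced them. For patients who withdraw, section 3.5 asks the investigator to "make every effort to complete the end-of-study evaluation".

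**The concern.** Whether a follow-up HbA1c exists is known only after the clinics have been randomised, and it can depend on the arm. Making it a condition of entry selects patients on a post-randomisation event. The natural reading is that efficacy analyses use the efficacy set. The missing-data rule is then applied to a group from which the patients with no follow-up HbA1c have already gone.

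Such patients are realistic. With no mandatory tests and with weeks 6 and 18 optional, someone lost before week 12 can easily have no post-baseline value.

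Unequal loss is plausible too. Section 4.4 has test clinics monitor flagged patients weekly and message those who do not measure glucose, while control clinics give no such management. Section 3.5, on the other hand, allows withdrawal for not following instructions about the software, which bears mainly on the test arm. Loss could lean either way. A trigger that looks for imbalance between groups exists to detect this, and as written it may miss the part of the imbalance that arises earliest.

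**Working it through.** **1. The plan's own figures (section 3.2, Rationale).** Inputs: difference 0.4, SD 1.1, two-sided 5%. Power is not in the readable text; 80%, 85% and 90% were tried, and a two-sample t-test gives totals of 240, 274 and 320. So 85% reproduces the stated 274. Design effect: 1 + (20 − 1) × 0.02 = 1.38. Then 274 × 1.38 = 378.1, and 378 / (1 − 0.20) = 472.5, or 473, against a target of about 480 (24 sites × 20). The sample size reproduces, and this point does not change it.

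**2. What the rule can see.** Assume that the planned 20% loss means 0.20 × 480 = 96 patients without a week-24 HbA1c. Let f be the share of those 96 with no post-baseline HbA1c at all. The protocol does not give f. Inside the efficacy set the visible missingness is 96(1 − f) / (480 − 96f):

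| f | Removed | Set size | Visibly missing | Visible rate |
|---|---|---|---|---|
| 0 | 0 | 480 | 96 | 20.0% |
| 0.25 | 24 | 456 | 72 | 15.8% |
| 0.50 | 48 | 432 | 48 | 11.1% |
| 0.75 | 72 | 408 | 24 | 5.9% |
| 1 | 96 | 384 | 0 | 0% |

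Judged against all enrolled subjects, the rate is 96/480 = 20% for every f. The removed group is larger than the visible one only if f exceeds 0.5.

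**3. The two readings of the entry condition.** If any post-baseline visit counts, patients with a value at week 6, 12 or 18 but none at week 24 stay in, can set off the rule and can be imputed; those with no value cannot. If the condition means a week-24 value, no primary outcome can be missing inside the set, and the rule has nothing to act on for the primary endpoint.

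**4. Effect on the estimate.** Let p be the proportion removed in an arm, and d the amount by which the removed patients' mean HbA1c change is worse than that of the patients retained. The full-arm mean is the retained mean + p × d. The full-set difference (test minus control) therefore equals the retained-set difference + (p_T × d_T − p_C × d_C). With the same d in both arms, the size of the shift is d × |p_C − p_T|. All rates and all values of d below are assumptions:

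| Removal in the two arms | d = 0.2 | d = 0.4 | d = 0.6 |
|---|---|---|---|
| Equal | 0 | 0 | 0 |
| 15% and 5% | 0.02 | 0.04 | 0.06 |
| 30% and 10% | 0.04 | 0.08 | 0.12 |

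Against the planned difference of 0.4, the non-zero entries run from 0.02/0.4 = 5% to 0.12/0.4 = 30%. If removed patients do worse and more controls are removed, the present set understates the benefit. If more test patients are removed, it overstates it.

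**5. A constructed case of hidden imbalance.** Suppose 5% of test and 25% of control patients have no post-baseline HbA1c, and 5% of those remaining in each arm lack week 24. The rule sees 5% against 5%. The actual loss is 1 − 0.95 × 0.95 = 9.75% against 1 − 0.75 × 0.95 = 28.75%, averaging 19.25%, close to the planned 20%. If all unobserved patients differ from observed ones by 0.4, the complete-case shift is (0.2875 − 0.0975) × 0.4 = 0.076. The documents support neither the five-fold gap nor the exact equality; the case shows only that the rule can be misled.

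**The case against.** General Principles ties neither the trigger nor the sensitivity analyses to the efficacy set. They could be run on all enrolled subjects without breaching any sentence, and a protocol often leaves the denominator and the imputation model to the SAP, which is not shown. This stands in part: one cannot say that the sensitivity analyses will miss these patients, only that nothing written brings them in. But the protocol has itself fixed both the set and the rule, and a SAP that followed it would inherit the gap.

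A reader might infer several stronger things that the documents do not support:

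- That the set and the rule cancel each other out. Unless the condition means week 24, patients with an interim value but no week-24 value stay in the set and the rule works for them.
- That the excluded patients are the main missing group. No split is given. The schedule marks week-12 laboratory tests without the option brackets used for weeks 6 and 18, and an end-of-study evaluation is to be attempted after withdrawal. Both would reduce the group, although tests still depend on routine care.
- That the present set favours the test arm. The direction depends on which arm loses more and on how those patients fare.

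It is also fair to say that imputing patients with baseline data alone, under missing at random, recovers little of any difference that baseline does not explain. That is a reason for adding delta-shift analyses, not for leaving these patients out.

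**Conclusion.** The concern holds as a gap in the rule. Entry to the only efficacy set depends on a post-randomisation outcome, and no wider set is defined. On the natural reading, patients with no follow-up HbA1c are outside both the judgement of missingness and the imputation.

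The size is unknown. Under the planned 20% loss, the visible rate can lie anywhere from 20% to 0%. The bias is zero if removal is equal and the removed patients differ from the retained ones by the same amount in both arms; under the assumed rates in the working it reaches 0.12 HbA1c points, in either direction. The conclusion rests on the wording and on taking the efficacy set as the population for efficacy analyses, not on any of the assumed rates. It merits a change because the present text can hide differential early loss and the repair is cheap.

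**What to change.** In the Efficacy Analysis Set paragraph, drop the post-baseline HbA1c condition for the primary analysis, and analyse eligible enrolled subjects by their clinic's allocation. The revised sentence should say explicitly whether the condition of at least one use stays; this point does not turn on it.

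In General Principles, state that:

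- missing week-24 HbA1c is measured per arm against all enrolled subjects;
- multiple imputation is run on the wider set, respects clinic clustering, and uses baseline and any interim values;
- delta-shift sensitivity analyses are run on the same set.

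Keep the present set as a supportive analysis.

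The cost is a few sentences in section 7.2 and slightly more programming. The estimate may move in either direction and be slightly less precise. No visit, test or change of sample size is needed.
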